**Statistical methods.** IBT and WLC groups will be compared on baseline characteristics using analyses of variance for continuous and chi-square tests for categorical variables. If characteristics differ significantly and are predictive of outcome, they will be considered as covariates in subsequent analyses. The primary outcome will be the percent of participants in IBT and WLC conditions with biochemically-confirmed illicit opioid abstinence at the 24-week assessment, evaluated based on a chi square test. Primary analyses will include all randomized subjects independent of early dropout and with missing urine specimens considered positive for illicit opioids, consistent with an intent-to-treat approach (Armitage, 1983). We hypothesize that participants receiving IBT will achieve significantly greater biochemically-verified illicit opioid abstinence relative to WLC. If applicable, logistic regression will be used to adjust for baseline covariates confounded with treatment group. Though not the primary outcome, abstinence at the other monthly assessments will be compared between groups with Bonferroni-adjusted chi square tests to control experiment-wise type I error rate below  $\alpha=.05$ . Within the IBT group, generalized estimating equation (SAS, PROC GENMOD) will be used to characterize the temporal trend in abstinence across monthly assessments. Additional outcomes will include IV opioid use, other (non-opioid) drug use, retention, BUP adherence, IVR utilization, and patient satisfaction. Repeated measures analyses of variance (SAS, PROC MIXED) will be used to compare groups on continuous outcomes (e.g., past-month frequency of illicit opioid and IV use, ASI subscales, BDI, HIV+HCV knowledge). If significant treatment by time interactions are detected, partial F-tests will be used to examine simple effects of treatment at each assessment. Additional repeated measures analyses will characterize temporal patterns in IBT-specific outcomes (e.g., BUP adherence, IVR utilization, satisfaction). Statistical analyses will be performed using SAS statistical software Version 9.4.

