**Sample size justification.** The proposed sample size is based on having sufficient power for detecting treatment differences for both primary and secondary outcomes. Regarding the primary outcome measure, the percent of participants negative for illicit opioids at the 24-week assessment, power is estimated to be greater than 95% using  $\alpha=.05$  if true abstinence rates are as low as 60% vs. 15% for IBT and WLC groups, respectively. These estimates are more conservative than our R34 outcomes, with lower abstinence predicted in IBT as we increase the duration to 24 weeks. Furthermore, power is estimated to be 80% or more to detect group differences as low as 30% in 24-week abstinence rates ( $ES=0.56$ ). For secondary outcomes, effect sizes range from small to moderate. The estimated mean

differences and minimum detectable effect sizes corresponding to 80% power ( $\alpha=.05$ ) for detecting treatment group differences in the change from baseline to Week 24 for representative ASI subscales are: Employment=.118 (ES=0.32), Psych=.107 (ES=0.51), Legal=.062 (ES=0.45), and Drug=.079 (ES=0.72). Similarly, power is 80% for detecting a mean difference of 5.5 units in the 24-week change in BDI (ES=0.42), which is smaller than we observed in our pilot trial. Lastly, power is estimated to be 80% to detect a mean absolute difference of 8.5% in the pre-post change in HIV knowledge scores (ES=0.54). It should be noted that these effect sizes (Cohen d's) are expressed relative to the between-subject variability at baseline [i.e.  $(\Delta_{IBT}-\Delta_{WLC})/\sigma_{\text{between-subject}}$ ], not the variability in the change scores [i.e.  $(\Delta_{IBT}-\Delta_{WLC})/\sigma_{\Delta}$ ] (Becker, 1988; Morris, 2008). The actual computation accounts for the correlation observed across repeated assessments for each outcome observed in our pilot data which is responsible for the different estimates of detectable ES's.

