### **Sample size justification**

The proposed sample size is based on having sufficient power for detecting treatment differences for primary and secondary outcomes. Regarding the percent of participants negative for illicit opioids at the 24-week assessment, power is estimated to be greater than 95% using  $\alpha=.05$  if true abstinence rates are as low as 60% vs. 15% for IBT and WLC groups, respectively. These estimates are more conservative than on our R34 outcomes, with lower abstinence predicted in IBT as we increase the duration to 24 weeks and move beyond a single research clinic for this Stage II trial. For secondary aims, effect sizes range from small to moderate. The estimated differences between conditions in mean change from baseline to 24 weeks corresponding to power=80% for representative ASI subscales are: Employment=.084 (ES=0.23), Psych=.076 (ES=0.36), Legal=.044 (ES=0.32), and Drug=.056 (ES=0.51). Similarly, power is 80% for detecting a mean difference of 4 units in the 24-week change in BDI (ES=0.30) which is smaller than we observed in our pilot trial. Lastly, power is estimated to be 80% to detect a mean absolute difference of 6% in the pre-post change in HIV knowledge scores (ES=0.39) and 5.5% (ES=0.34) for the pre-post change in OD knowledge scores. It should be noted that these ES's (Cohen d's) are expressed relative to the between-subject variability at baseline [i.e.  $(\Delta_{IBT}-\Delta_{WLC})/\sigma_{\text{between-subject}}$ ], not the variability in the change scores [i.e.  $(\Delta_{IBT}-\Delta_{WLC})/\sigma_{\Delta}$ ] (Becker, 1988; Morris, 2008). The actual computation accounts for the correlation observed across assessments for each outcome observed in our pilot data which is responsible for the different estimates of detectable ES's.

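### The 80% power for ASI and BDI refers to change from baseline to Week 24, a contrast the analysis text never names; the Week 24 simple effect it names has about 35-72% power for four of the five outcomes, before its interaction gate

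*Supplement*

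**What the plan says.** Trial 1, Sample size justification, lists minimum detectable differences at 80% power and alpha .05 "for detecting treatment group differences in the change from baseline to Week 24": "Employment=.118 (ES=0.32), Psych=.107 (ES=0.51), Legal=.062 (ES=0.45), and Drug=.079 (ES=0.72"). For depression, "power is 80% for detecting a mean difference of 5.5 units in the 24-week change in BDI", with ES 0.42. It adds that "these effect sizes (Cohen d's) are expressed relative to the between-subject variability at baseline", not to the SD of the change scores, and that the pilot correlation across assessments entered the computation and explains why the detectable effects differ between outcomes.

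Trial 2, Sample size justification, does the same at 100 per arm: "The estimated differences between conditions in mean change from baseline to 24 weeks corresponding to power=80"% are given as ES 0.23 (Employment), 0.36 (Psychiatric), 0.32 (Legal) and 0.51 (Drug), with BDI 4 units (ES 0.30).

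Statistical methods, in both trials, plans repeated-measures ANOVA in PROC MIXED for continuous outcomes, followed by: "If significant treatment by time interactions are detected, partial F-tests will be used to examine simple effects of treatment at each assessment". Neither section names a baseline-to-Week-24 contrast. Neither prespecifies the baseline score as a covariate; covariates enter only if they differ significantly between arms and predict outcome.

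**The concern.** The contrast that was powered and the follow-up test that was planned are different statistics. The difference in change has variance 2σ²·2(1−ρ)/n, which shrinks as the baseline-to-Week-24 correlation ρ rises. A simple effect at Week 24 has variance 2σ²/n whatever ρ is. The printed effect sizes below about 0.57 (50 per arm) or 0.40 (100 per arm) reach 80% power only because of ρ, so the planned Week 24 test cannot deliver that power. It is also run only if an omnibus interaction is significant.

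Both trials say the sample size was chosen with secondary as well as primary outcomes in mind, so the stated 80% is part of the design rationale. A team following the text as written could report a Week 24 benefit of the stated size as not shown, or not test it.

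**Working it through.** **Inputs.** Effect sizes, 80% power and alpha .05 are from the two Sample size justification sections. There are 50 per arm (Trial 1) and 100 per arm (Trial 2). Assessments are at intake and Weeks 4, 8, 12, 16, 20 and 24. Assumed, because not stated: two-sided test, Week 24 SD equal to baseline SD, no dropout.

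**Step 1: reproduce the plan's 80%.** By noncentral t, the standardised difference detectable with 80% power is 0.566 at 50 per arm and 0.398 at 100 per arm. For a change-score test on the baseline-SD scale, ES = d·√(2(1−ρ)), so ρ = 1 − (ES/d)²/2. For Employment in Trial 1: 1 − (0.32/0.566)²/2 = 0.84.

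| Outcome | ES, Trial 1 / 2 | Implied ρ, Trial 1 / 2 | Implied baseline SD, Trial 1 / 2 |
|---|---|---|---|
| Employment | 0.32 / 0.23 | 0.84 / 0.83 | 0.369 / 0.365 |
| BDI | 0.42 / 0.30 | 0.72 / 0.72 | 13.1 / 13.3 |
| Legal | 0.45 / 0.32 | 0.68 / 0.68 | 0.138 / 0.137 |
| Psychiatric | 0.51 / 0.36 | 0.59 / 0.59 | 0.210 / 0.211 |
| Drug | 0.72 / 0.51 | 0.19 / 0.18 | 0.110 / 0.110 |

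The correlations are back-solved, so Trial 1 alone proves nothing. The check is that Trial 2, at twice the sample size, gives nearly the same values. A baseline-adjusted comparison does not fit: Drug would need a residual SD of 0.72/0.566 = 1.27 times the baseline SD. The printed 80% is therefore consistent with a 1-df test of change.

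**Step 2: the planned Week 24 simple effect.** The noncentrality is ES·√(n/2). For Employment in Trial 1 it is 0.32 × √25 = 1.60, giving 35%.

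| Outcome | Stated | Trial 1, 50 per arm | Trial 2, 100 per arm |
|---|---|---|---|
| Employment | 80% | 35% | 37% |
| BDI | 80% | 55% | 56% |
| Legal | 80% | 61% | 62% |
| Psychiatric | 80% | 71% | 72% |
| Drug | 80% | 95% | 95% |

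**Step 3: the interaction gate, Trial 1.** If intake is a level of time, two arms by seven occasions gives 6 df. Under compound symmetry the noncentrality is (n/2)·Σ(δₜ − mean δ)²/(1−ρ), where δₜ is the standardised arm difference at occasion t. From Step 1, ES²/(1−ρ) = 2 × 0.566² = 0.640 for every outcome. An effect present in full from Week 4 (or only at Week 24) gives 25 × 0.640 × 6/7 = 13.7. A linearly growing effect gives 25 × 0.640 × 28/36 = 12.4. With F(6, 588) the power is about 80% and 75%.

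**Step 4: both steps together.** Simulation under compound symmetry (200,000 runs, same three profiles) gives, for a significant gate and a significant Week 24 effect: Employment 30-32%, BDI 45-50%, Legal 50-54%, Psychiatric 58-63%, Drug 73-79%.

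**Step 5: the reduced target.** Trial 1's change summary sets the target at 50; Trial 2's says its sample was cut to align. At an assumed 25 per arm, the detectable ES for a Week 24 simple effect is 0.81. The change contrast at the printed Trial 1 effects has about 50% power.

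**The case against.** The strongest reply is that the planned ANOVA does test differential change. The treatment-by-time interaction uses the within-person correlation and, under compound symmetry, has about 75-80% power, close to the stated figure. That stands: a reader might infer that the analysis throws away the within-person information, and for the omnibus step it does not. The loss lies mainly in the follow-up step that would locate an effect at Week 24. The omnibus test does not isolate Week 24, so it is no substitute for the powered contrast.

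A reader might also infer that effects of the stated size will usually be missed. At 50 per arm only Employment clearly supports that. The plan examines every visit: under compound symmetry with an immediate effect, passing the gate and finding at least one significant visit has about 66% power for BDI, 71% for Legal and 76% for Psychiatric, without multiplicity adjustment.

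Adjusting Week 24 for the baseline score would give about 83-96% power at 50 per arm, but the conditional covariate rule does not commit to that.

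Finally, these are secondary outcomes, and the printed effects are minimum detectable differences rather than expected ones. For BDI the plan says 5.5 units is smaller than the pilot difference. The primary endpoint is untouched. This limits the stakes but does not remove the mismatch.

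**Conclusion.** The point holds as a mismatch between the power statement and the named tests, in both trials and at their printed sample sizes. The Week 24 simple effect alone has about 35-37% (Employment), 55-56% (BDI), 61-62% (Legal) and 71-72% (Psychiatric) power where 80% is stated; Drug, at 95%, is adequate before the gate.

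The 35-72% range should not be read as the power of the whole procedure. It excludes the gate, and with both steps required all five outcomes fall below 80% under compound symmetry in Trial 1.

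The results rest on equal SDs at baseline and Week 24, no dropout, a two-sided test and back-solved correlations. The 6 df is inferred, since the plan does not say whether intake is a level of time. The covariance structure is also not given; under AR(1) the gate's power could run from about 52% to over 99%, depending on outcome and effect profile.

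A reader might also infer that naming the right contrast secures 80% power. At the reduced target it does not. The cut in sample size is a separate matter.

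**What to change.** In Statistical methods of both trials, prespecify as the main test for the ASI subscales and BDI the 1-df contrast (IBT Week 24 minus baseline) minus (WLC Week 24 minus baseline). Take it from the planned PROC MIXED model with intake as a level of time, using an ESTIMATE statement. Report it with its 95% CI whether or not the interaction is significant, and keep the interaction and per-visit tests as descriptive.

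The cost is a sentence of text and one statement in a model already being fitted, with no added participants or data. The per-visit tests lose confirmatory standing.

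If the gated simple effects are kept instead, restate the detectable effects in both Sample size justification sections for that test at the sample size in force: about 0.57 at 50 per arm, 0.40 at 100 per arm, or 0.81 at 25 per arm (target of 50, 1:1 allocation assumed). All are before the gate, so the text should say that power for the full procedure is lower. Under either option, the power statement should be reissued for the reduced target.

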#### Potential Benefits to Participants and Others

Volunteers may benefit by initiating abstinence from illicit opioids during their study participation, including experiencing a reduction in the wide range of medical, financial, psychosocial, and legal consequences associated with illicit opioid abuse. By improving treatment access for opioid abuse and dependence, the proposed research also stands to benefit public health in general by reducing the vast economic and societal costs associated with opioid abuse (e.g., health service utilization and costs, criminal activity, contraction of preventable diseases such as HIV and hepatitis). In addition, there are potential scientific benefits to be gained by expanding our empirical knowledge on how to mitigate gaps in treatment access among opioid-dependent individuals. Overall, the individual participant, the medical and scientific communities, and society in general may benefit by our efforts to develop an interim buprenorphine treatment for patients awaiting agonist maintenance. As such, the risks to which individuals may be exposed as a function of their research participation are reasonable in relation to the anticipated benefits.

#### Importance of the Knowledge to be Gained

The proposed project has the potential to contribute a novel and effective technology-assisted pharmacotherapy protocol that can be widely disseminated to bridge gaps in access to life-saving opioid treatment. Thus, knowledge gained from this research may significantly enhance the accessibility, implementation and effectiveness of drug abuse treatment more generally. Consequently, the risk/benefit ratio is favorable. The risks to which individuals are exposed as a consequence of their research participation are generally less than that associated with continuing their ongoing abuse of illicit opioids. In contrast, the potential and probable benefits to be derived by society in general and by opioid abusers as a group are considerable. In summary, conducting this research seems well justified.

**Therapeutic Alternatives:** *List the therapeutic alternatives that are reasonably available that may be of benefit to the potential subject and include in the consent form as well.*

#### ☐ **Not Applicable**

Participants are free not to participate in this study or to withdraw from it at any time. If they decide not to participate in the study, we will be glad to discuss with them other treatments that may be available in Vermont, including residential, outpatient, and medication-assisted treatment options.

**Data Safety and Monitoring:** *The specific design of a Data and Safety Monitoring Plan (DSMP) for a protocol may vary extensively depending on the potential risks, size, and complexity of the research study. For a minimal risk study, a DSMP could be as simple as a description of the Principal Investigator's plan for monitoring the data and performance of safety reviews or it could be as complex as the initiation of an external, independent Data Safety and Monitoring Board (DSMB). The UVM/UVM Medical Center process for review of adverse events should be included in the DSMP.*

**Patient eligibility and status.** All intake data collection will be conducted by a trained bachelor's-level Research Assistant (RA) using specialized forms and procedures. Medical screening data will be reviewed by the Study Physician. All intake information will be reviewed by the PI, who will determine participant eligibility. Only trained and IRB-approved research staff will complete informed consent with eligible and willing participants. The status of all active participants will be reviewed at weekly meetings between the PI, Co-investigators and RAs.

**Rigorous data management/Quality assurance.** The majority of study data collection will be conducted using self-report questionnaires. Randomly selected data will be checked by the RAs for completeness and to ensure quality (i.e., no appearance of rote answers, etc.). In terms of standard operating procedures at the clinic, all assessments will be administered by trained research staff. All subject data will be maintained in secure filing cabinets behind locked doors in order to protect confidential subject information. Safe places will include locked filing cabinets or locked rooms that will be accessible

only to study personnel. Full subject names will not be listed on the outside of the binders in order to protect the identity of study participants. Moreover, all data that are entered into spreadsheets and databases, in preparation for data analyses, will be entered twice. That is, two separate individuals will enter the data into databases, and a comparison between data entries will be conducted to detect data entry errors. All discrepancies in data entry will be checked against the raw data source, and the correct data entry will be used. All data that are entered into spreadsheets and databases will be coded by subject ID number and not by subject name. Additionally, all entered data will be backed up on an external hard drive or a secure project server at least weekly. The biostatistician and PI will discuss any problems at monthly data meetings. Additional meetings will be conducted on an as-needed basis. An original copy of the data will be retained at the clinic should anything happen to the document during transmission.

**Auditing procedures.** Review of any problems related to quality of data collection, transmission or analyses and of any AEs and SAEs that occurred during the past week will occur at weekly research staff meetings. Interim analyses of efficacy data will be conducted when half the subjects have been entered or at other times based on the joint discretion of the PI, Co-I and biostatistician.

**Adverse Event and Unanticipated Problem (UAP) Reporting:** *Describe how events and UAPs will be evaluated and reported to the IRB. All protocols should specify that, in the absence of more stringent reporting requirements, the guidelines established in the Committees on Human Research "Adverse Event and Unanticipated Problems Reporting Policy" will be followed. The UVM/UVM Medical Center process for review of adverse events and UAPs to subjects or others should be included in the DSMP.*

AEs and SAEs will be assessed at each clinic visit by a trained RA or nurse. Any SAE will be brought to the attention of the PI as soon as possible and not longer than 24 hrs. Any SAE, whether or not related to study intervention, will be reported to the IRB using the UVM Adverse Event Reporting Document within 5 days of the event. The IRB will make a determination as to whether additional reporting requirements are needed. Any SAEs will also be summarized in the yearly IRB continuing review, including a review of frequency and severity.

**Withdrawal Procedures:** *Define the precise criteria for withdrawing subjects from the study. Include a description of study requirements for when a subject withdraws him or herself from the study (if applicable).*

Completing study visits and providing urine specimens as scheduled are necessary in order for subjects to receive the study medication. Thus, if the subject fails to attend scheduled visits, or does not submit regularly scheduled urine specimens, or if there is any evidence of nonadherence to the medication regimen, they will be withdrawn from the study. If they are discharged from the study, subjects will be expected to return all remaining medication and the Med-O-Wheel device to study staff immediately. Females will be tested for pregnancy prior to and during the study. Should a subject become pregnant during the trial, her participation will be terminated and she will be assisted with accessing treatment at the medical center's high-risk pregnancy clinic.

Patients are free not to participate in this study or to withdraw from it at any time. If they decide not to participate in the study, we will be glad to discuss with them other treatments that may be available in Vermont, including residential, outpatient, and medication-assisted treatment options. If patients decide not to participate or to withdraw from this study, their decision will not prejudice their future medical care at UVM or UVM Medical Center.

**Sources of Materials:** *Identify sources of research material obtained from individually identifiable human subjects in the form of specimens, records or data. Indicate whether the material or data will be obtained specifically for research purposes or whether use will be made of existing specimens, records or data.*

Research materials will include questionnaires, structured clinical interviews, expired air samples for analyzing breath alcohol levels, urine samples for analyzing recent drug use and pregnancy status. All data will be collected for research purposes only. All data collection will be conducted by a trained bachelor's-level Research Assistant (RA) with special training on all forms and procedures. All information will be reviewed by the PI, who will determine participant eligibility and complete informed consent with eligible and willing participants. Subject data will be maintained in secure filing cabinets behind locked doors in order to protect confidential subject information. Safe places will include locked filing cabinets or locked rooms that will be accessible only to study personnel. Full subject names will not be listed on the outside of the binders in order to protect the identity of study participants. Subject data and subject identifiers will only be accessible to approved research staff.

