***Buprenorphine via computerized dispensing.*** IBT participants will receive buprenorphine/naloxone sublingual tablets (Amneal Pharmaceuticals, Bridgewater, NJ), which will be obtained through our university hospital's investigational pharmacy. Induction will occur in Week 1, with individualized dose adjustments at daily visits determined using the Clinical Institute Narcotic Assessment (Peachey & Lei, 1988) with the aim of stabilizing participants on a dose sufficient to achieve withdrawal suppression without intoxication or sedation. We have successfully used these procedures in our prior BUP studies ([name] et al., 2009, 2013, 2015c, 2016). At each visit, the research nurse will assess withdrawal and agonist effects and the RA will collect urine and breath samples. During stabilization, the RA will also instruct IBT participants on how to use the IVR system and Med-O-Wheel and have them complete HIV+Hepatitis Education (described below). Following stabilization, participants will visit the clinic every two weeks (i.e., Weeks 2, 4, 6, etc.) to provide a urine specimen, ingest that day's dose under nurse observation, and complete measures of opioid and other drug use via Time-Line Followback. They will receive the doses for the upcoming 13-day interval in the Med-O-Wheel (Addoz, Forssa, Finland) for ingestion at home. Participants will be instructed to bring the device with them to each study visit and reminded throughout the study that nonadherence may be grounds for discharge. Participants can also return to the clinic between scheduled visits should any concerns arise or a dose evaluation be needed.

***IVR daily monitoring.*** The IVR system will contact participants each evening at a convenient time identified by them to assess any opioid, other drug or alcohol use, as well as opioid craving and withdrawal. Instances of use, craving or withdrawal will prompt additional detailed questions (e.g., type and amount used, severity of craving and withdrawal), as well as provision of information about support meetings taking place in the community. Participants can make inbound calls to the system at any time to complete their daily check-in if they anticipate missing the call or if it is more convenient. They can also reach study staff at any time on our on-call mobile phone.

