Following stabilization, participants will visit the clinic every two weeks (i.e., Weeks 2, 4, 6, etc.) to provide a urine specimen, ingest that day's BUP dose under nurse observation, and complete measures of opioid and other drug use via Time-Line Followback. They will receive the doses for the upcoming interval in a Med-O-Wheel device (Addoz, Forssa, Finland) for ingestion at home. The Med-O-Wheel is a portable pill dispenser with tamper resistant features. Participants will be instructed to bring the device

with them to each study visit, as well as random call-backs (below) and reminded throughout the study that any evidence of nonadherence may be grounds for discharge. Participants can also return to the clinic between scheduled visits should any concerns arise or a dose evaluation be needed. Research staff will work with IBT participants throughout the trial to line up a provider for continued treatment in the community following the study. If a treatment slot is available, we will coordinate a smooth transfer to that program to begin the day following the Week 24 assessment.

**IVR daily monitoring.** The IVR system will contact participants each evening at a convenient time identified by them to assess opioids and other drug or alcohol use, as well as opioid craving and withdrawal. Instances of use, craving or withdrawal will prompt additional detailed questions (e.g., type and amount used, severity of craving and withdrawal), as well as provision of information about support meetings taking place in the community. Participants can make inbound calls to the system at any time to complete their daily check-in if they anticipate missing the call. They can also reach study staff at any time using our on-call mobile phone.

**Random call-backs via IVR.** Participants will be contacted via IVR approximately twice per month (once per two-week dosing interval) on a random basis and instructed to return to the clinic within 12 hours. For each random call-back, they will refrain from taking that day's dose and instead bring in their Med-O-Wheel device to ingest their medication under nurse observation. The research nurse will conduct a pill count and inspect the device for any evidence of tampering or nonadherence, and participants will provide breath and urine specimens (see Biochemical monitoring).

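### Both trials give two rules for nonadherence (discharge possible, or withdrawal automatic), and neither says whether a withdrawn participant still gives a Week 24 urine that would otherwise be scored positive

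*Supplement*

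**What the plan says.** **Treatment section.** Under the heading on buprenorphine via computerized dispensing, Trial 1 participants are to be reminded that "nonadherence may be grounds for discharge". Trial 2 has the same reminder with a wider trigger: "any evidence of nonadherence may be grounds for discharge".

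**Withdrawal Procedures.** Both protocols open with "Completing study visits and providing urine specimens as scheduled are necessary in order for subjects to receive the study medication". They then list missed scheduled visits, missed scheduled urines and nonadherence, the last in these words: "if there is any evidence of nonadherence to the medication regimen, they will be withdrawn from the study". The next sentence begins "If they are discharged from the study, subjects will be expected to return all remaining medication", so discharge and withdrawal are used for the same event.

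**Analysis.** In Statistical methods for Trial 1 the primary outcome is "illicit opioid abstinence at the 24-week assessment, evaluated based on a chi square test". The analysis set is described as follows: "Primary analyses will include all randomized subjects independent of early dropout". It is to be run "with missing urine specimens considered positive for illicit opioids". Trial 2 has the same set and missing-data rule, with a site-stratified Cochran-Mantel-Haenszel test.

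Neither protocol sets a threshold for nonadherence, provides for assessment after a withdrawal by staff, or allows for withdrawals in the sample size. Neither summary of changes touches these points.

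**The concern.** One text leaves discharge to judgement and the other makes it follow from any evidence of nonadherence. Two staff members could handle the same participant differently, and both could point to the protocol.

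This reaches the primary endpoint. A participant withdrawn from the study may have no Week 24 specimen and would then be scored positive whatever their true status. Only IBT participants have a medication regimen, pill counts and device inspections, so the medication trigger cannot fall on the waitlist arm (WLC). The protocol's own rule may therefore create missing outcomes mostly in one arm. How many depends on which sentence is followed. At stake are the size of the estimated effect and the power. A false claim of benefit is not at stake, because the bias runs against IBT.

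**Working it through.** **Inputs**
- Planning rates 60% (IBT) and 15% (WLC), α = .05, power above 95%: Sample size justification. A two-sided test is assumed.
- 50 per arm: Number of Subjects, Trial 1. The Trial 1 summary of changes revises the target to 50, which is 25 per arm if that is a total split 1:1 (assumption). The Trial 2 body text has 100 per arm, but its summary of changes aligns the size with Trial 1.
- Pilot: 99% of doses taken, 96% of random call-backs met, IBT retention 92% over 12 weeks: Supporting preliminary data.
- 24 weeks of daily dosing = 168 doses. About one call-back per two weeks = 12.

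**The plan's own figure.** Exact power of the uncorrected chi-square for 60% vs 15% is 99.9% at 50 per arm, which agrees with the stated figure. At 25 per arm it is 94.1%.

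**Effect of withdrawals unrelated to true status.** Let w be the share of IBT withdrawn, not assessed at Week 24 and scored positive. The IBT rate becomes 0.60 × (1 − w) and WLC stays at 15%. Site stratification in Trial 2 is ignored.

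| w | IBT rate | Difference | Power, 50 per arm | Power, 25 per arm |
|---|---|---|---|---|
| 0 | 60% | 45 points | 99.9% | 94.1% |
| 10% | 54% | 39 points | 99.0% | 86.5% |
| 20% | 48% | 33 points | 95.8% | 74.5% |
| 39% | 36.6% | 21.6 points | 71.1% | 43.4% |

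At 25 per arm one participant is 1/25 = 4 points.

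**Where 39% comes from.** If the pilot rates carry over and lapses are independent, 1 − 0.96^12 = 39% would miss at least one call-back. For doses, 1 − 0.99^168 = 82% would miss at least one.

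**Check against the pilot.** The same arithmetic over 12 weeks gives 1 − 0.96^6 = 22% with a missed call-back and 1 − 0.99^84 = 57% with a missed dose. Yet 92% of pilot IBT participants were retained. Either lapses clustered in a few people or a one-miss rule was not applied. So 39% is an upper-end illustration, and the dose figure is not a credible forecast.

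**Best case.** If withdrawals fall first on the 40% of IBT who would test positive anyway, the scored rate is min(0.60, 1 − w). Nothing is lost up to w = 40%. At w = 50% the rate is 50% and the difference 35 points.

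**The case against.** **The reminder is only a warning.** The treatment section reports what participants are told, while Withdrawal Procedures answer the form's request for precise criteria and may be taken to govern. This is fair, but the plan never says so, and the Trial 2 reminder uses the same trigger, any evidence, with a discretionary consequence.

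**Loss of the Week 24 urine is inferred.** A reader might conclude that the plan forbids the specimen after withdrawal. It does not say that. The rule is introduced through receipt of medication and followed by return of medication and device, so discharge from treatment alone is a possible reading. What stands is that the words used are withdrawal from the study and that nothing provides for later assessment.

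**Intent-to-treat is not breached.** A reader might see a conflict with an analysis of all randomised participants. There is none: the missing-as-positive rule covers withdrawals. The objection stands, and the remaining point is that outcomes are assigned rather than observed.

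**The rule is not wholly confined to IBT.** The missed-visit and missed-urine triggers refer to the subject and could be read to reach WLC at monthly assessments. Only the medication trigger is clearly IBT-only.

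**The size is weakly grounded.** No text equates a missed random call-back with nonadherence to the medication regimen, and Trial 1 lets the call-back window be individualised. The 60% is set below the pilot's 68% at Week 12 and may already absorb some dropout, so subtracting again may double count. Much of the low power at 25 per arm comes from the smaller sample. All of this stands. It limits the size of the loss but does not remove the contradiction or the silence on follow-up.

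**Conclusion.** The point holds as a contradiction in both trials together with an unstated rule for assessment after withdrawal. As written, it can replace observed Week 24 outcomes with assigned positives, mainly in IBT, and pull the estimate toward no difference.

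The loss may be nil, either because few are withdrawn or because those withdrawn would have tested positive anyway. At the upper end shown, the difference falls from 45 to about 22 points, with power of 71% at 50 per arm or 43% at 25 per arm. That end requires strict enforcement, no Week 24 specimen, withdrawals unrelated to true status, independent lapses and missed call-backs counted as nonadherence. The 25-per-arm figure also assumes that the revised target of 50 is a total split 1:1.

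A reader might infer that the rule will remove most of the treatment effect. The documents do not support that as a forecast, and pilot retention of 92% speaks against it. The contradiction is certain and the size is not. It should be corrected because the correction is cheap and prevents missing data that the protocol itself may cause.

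**What to change.** 1. In each trial, reconcile the treatment section with Withdrawal Procedures so that one rule on nonadherence applies. The choice of rule is for the investigators.
2. Whichever rule is kept, define two separate events: study medication stopped, and withdrawn from the study.
3. Continue the monthly assessments and the Week 24 urine for every randomised participant who has not withdrawn consent, including those whose medication has been stopped. Missing-as-positive then applies only to specimens that could not be obtained.
4. Report by arm how many were stopped under the rule and how many of them gave a Week 24 specimen.

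The cost is protocol wording and a few extra paid assessments. The primary outcome, test and analysis set do not change.
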